## Abstract

**Introduction:**

Periodontitis is highly prevalent and disproportionately affects vulnerable populations, including older adults, racial and ethnic minorities, and low-income individuals. While periodontal therapies are largely effective, patient engagement in periodontal care is problematic. The study describes in this protocol aims to identify the top ten research priorities or uncertainties for specialized periodontal care (SPC) that are most important to periodontal patients and care providers.

**Methods:**

The James Lind Alliance approach will guide the priority-setting partnership (PSP), which involves several steps: forming a PSP steering committee, gathering potential research uncertainties, summarizing the research uncertainties, verifying unanswered uncertainties, completing an interim priority setting survey, and facilitating a priority setting workshop. Study participants will be periodontal patients (n ~ 150) and care providers (n ~ 120), including general dentists, periodontists, and dental hygienists in Alberta, Canada. A steering committee representing the four stakeholder groups will oversee the study. Data on uncertainties from these groups will be gathered through two online surveys and focus groups. Demographic data (*e.g.,* age, sex) will be collected to describe participants and ensure representation of all stakeholder groups. Uncertainties submitted by participants will be evaluated against the existing evidence gathered through a scoping review to determine if they have already been addressed. Unanswered uncertainties will be taken to a workshop where participants (n ~ 20) representing all the stakeholder groups will set the top ten research priorities. Data analysis will include descriptive statistics and content analysis. The study is expected to conclude in August 2026.

**Conclusion:**

Study findings will be disseminated to raise awareness among researchers and funders on research priorities that matter most to patients and dental care providers regarding patient engagement in SPC.

## Introduction

Periodontitis is highly prevalent, has adverse consequences for individuals and healthcare systems, and disproportionally affects vulnerable populations. Periodontitis is the sixth most prevalent disease worldwide [1]. Nearly half of adults in the United States have periodontitis [2], and one-quarter of adults in Canada suffer from severe periodontitis [3]. This condition has adverse, long-lasting consequences for individuals, including tooth loss, impaired masticatory function, nutritional compromise, altered speech, low self-esteem, and sub-optimal quality of life [4–6]. Periodontitis has been associated with non-communicable chronic conditions such as cardiovascular disease and diabetes mellitus [7]. Periodontitis also imposes a substantial financial burden on individuals and healthcare systems based on both direct and indirect costs [8]. Several groups are particularly impacted by this condition, including older adults, low-income individuals, racial and ethnic minorities, and people with disabilities. These groups also experience elevated levels of untreated dental conditions [9,10].

Available therapies, both non-surgical and surgical, are largely effective in managing periodontitis. Regular patient education emphasizing the importance and proper implementation of home care of biofilm removal has been effective in preventing and managing periodontitis as evidenced by improvements in plaque index and gingival index [11]. Research has consistently reported positive clinical outcomes (e.g., pocket probing reduction, clinical attachment level gain) when local and systemic antibiotics are used as adjunctive therapy to scaling and root planing in the treatment of moderate to severe periodontitis [12,13]. Traditional periodontal surgery effectively reduces periodontal probing depth and enhances periodontal architecture, while emerging approaches hold promise for halting periodontitis and promoting periodontium regeneration [14]. Periodontal treatment can also enhance non-clinical outcomes, such as oral health-related quality of life [15].

Patients can benefit from periodontal therapies if they optimally engage in periodontal services [13,16]. Patient engagement in health services broadly refers to the process of seeking and utilizing these services, including whether, how, why, and for how long the services are used [17]. Active engagement of patients has been found to improve health behaviors, clinical outcomes, quality of life, quality and efficiency of services, and patient empowerment [18,19]. Research has shown that adherence to periodontal treatment improves outcomes, including a reduction in biofilm and gingival bleeding rates [16,20]. Negative outcomes, such as increased probing depth and tooth loss, have been associated with poor adherence to clinical appointments, with adherence to periodontal supportive therapy ranging from 2% to 64% [21,22].

The available literature on patient engagement in periodontal care is limited, outdated, and inconclusive. Most original research on this topic has used quantitative approaches and focused on referral and adherence to periodontal care. Research on referral has largely centered on demographic predictors related to patients (e.g., socioeconomic status, type of dental insurance) and referral providers (e.g., age, gender, location), which falls short of revealing the complexity of the referral process [23,24]. Similarly, most research on patient adherence has focused on rates and predictors of appointment-keeping during the maintenance phase in general practice, such as age, smoking status, and disease severity [25,26]. Predictors and factors influencing patient involvement during the diagnosis and active treatment phases in settings such as dental school clinics have been relatively understudied. Three recent reviews indicated that the majority of studies on periodontal referral and adherence were published in 2010 or earlier [16,22,24]. Although limited in scope and depth, these reviews concluded that the available evidence is insufficient for understanding and improving patient engagement in periodontal care.

Currently, there is a need for expanding and enhancing the scope and relevance of research on patient engagement in periodontal care. To address this need, the involvement of healthcare stakeholders, especially patients and care providers, as equal partners is paramount [27,28]. This study aims to identify the top ten research priorities or uncertainties for patient engagement in specialized periodontal care (SPC) by gathering insights from periodontal patients and care providers, including general dentists, periodontists, and dental hygienists. This study will seek to answer the following questions: What are the top ten research priorities for periodontal patients and care providers regarding patient engagement in SPC? What are the issues regarding patient engagement in SPC that matter most to periodontal patients and care providers? The study findings will be important for guiding future research directions and optimizing the allocation of financial resources through both public and private funding.

## Materials and methods

### Design

The study design will be guided by the James Lind Alliance (JLA) approach, which includes the following steps: *(1)* forming a priority setting partnership (PSP) steering committee, *(2)* gathering potential research uncertainties, *(3)* summarizing the research uncertainties, *(4)* verifying unanswered uncertainties, *(5)* completing an interim priority setting survey, and *(6)* facilitating a priority setting workshop [27]. As a partnership-driven approach [29], the James Lind Alliance (JLA) is well-suited to identify relevant research priorities for both practice and science through collaboration with healthcare stakeholders, particularly patients, caregivers, and care providers. In recent years, this inclusive approach has been successfully used to set research priorities for several chronic conditions, including diabetes [30], dementia [31], Parkinson [32], chronic kidney [33], and eating disorders [34]. The study is expected to conclude in August 2026. Fig 1 illustrates all the steps of the PSP, including the scoping review that will support this process.

**Fig 1 pone.0319841.g001:**
[figure not shown]
Flow chart of the PSP for patient engagement in SPC, including a scoping review.

### Research setting and participants

The study is expected to be conducted over a two-year period, from September 2, 2024 to August 31, 2026, and will involve periodontal patients and care providers in Alberta, Canada. Former and active periodontal patients, general dentists, periodontists, and dental hygienists practicing in Alberta for at least three years will be eligible to participate. Sample size estimates are not calculated for JLA-PSP projects [27]; however, based on previous similar studies [33,35,36], we estimate the enrollment of ~ 150 patients, ~ 60 general dentists, ~ 20 periodontists, and ~ 30 dental hygienists. Several recruitment strategies will be employed. Patients will be approached in person in clinical settings and contacted using clinic registries. They will also be informed about the study through local advertisements (e.g., posters), social media, and grassroots agencies. These strategies will help reach groups that have been historically marginalized and disproportionally affected by periodontal diseases. Care providers will be reached in person and through professional organizations’ communication channels (e.g., email lists, newsletters), social media (e.g., specific websites and platforms), local advertisements, and individual networks. Patients and care providers will be encouraged to invite other eligible participants.

### Step 1. Forming a PSP steering committee (SC)

This committee will oversee all study activities to ensure adherence to the JLA process. Representation of all stakeholder groups will be achieved by recruiting 2 patients, 2 general dentists, 2 periodontists, and 2 dental hygienists. SC members will be offered tokens of appreciation (e.g., $25 gift card) for their participation in the meetings (n = 6) over the course of the project. Three research team members will join the SC. Meetings will take place every three months via Zoom, lasting approximately two hours. Minutes will be taken to document decisions, including any remedial actions needed to address issues related to study implementation, ensure adherence to the JLA process, and track the implementation of suggested changes in subsequent meetings.

### Step 2. Gathering potential research uncertainties through survey and focus groups

An online survey using REDCap will be used to collect uncertainties, concerns, and issues that periodontal patients, general dentists, periodontists, and dental hygienists would like to be answered by research. The survey will be informed by the literature on data collection of uncertainties from stakeholders, following the JLA-PSP approach [27,28]. A total of five open-ended questions will be included, allowing respondents to elaborate on uncertainties and issues that matter to them. For example, respondents will be asked, ‘What questions and concerns would you like researchers to address regarding patient compliance with periodontal treatment?’ There will be no limit on the number of uncertainties respondents can suggest. The online survey will be available until saturation is reached, defined as the point when no substantially new uncertainties are suggested. To maximize participation, several strategies will be implemented. These include offering a $10 gift card as an incentive, clearly communicating the study’s benefits for patients, care providers, health services, and future research in the information letter, and collaborating with community agencies, clinical sites, and professional organizations. Additionally, reminder notifications will be sent to encourage participation throughout the survey period.

Five focus groups with patients and six with different care provider groups (~7 participants in each focus group) will be conducted via Zoom or in-person, depending on participant preferences, and recorded to facilitate data analysis afterwards. These focus groups will explore their perspectives on research priorities and engagement issues. Focus group participants will receive tokens of appreciation (e.g., $25 gift card) for their participation. Interview guides will be informed by previous studies and general guidelines for conducting focus groups [37]. Table 1 presents the main six focus group questions for patients. Similar follow-up questions will be asked for each main question, such as: ‘What aspects worked well or did you like?’ ‘What were the main issues or challenges, if any?’ and ‘What would you like researchers to explore about this particular topic?’ Focus group questions for care providers will vary based on their type and level of involvement in periodontal care. For example, referral providers such as general dentists and dental hygienists will be asked, ‘What has been your experience with referring patients to periodontal care?’ Table 2 outlines the main questions that will be asked to all periodontal care providers.

**Table 1 pone.0319841.t001:** Summary of the main focus group questions for patients.

How would you briefly describe your experience with getting and using periodontal care? What was it like for you to be referred to periodontal care? What happens at your first appointment when your periodontist checked your gum health? How was it for you to attend the other appointments? What has it been like to follow your periodontist’s advice? Overall, how would you describe your communication with your periodontist?

**Table 2 pone.0319841.t002:** Summary of the main focus group questions for care provider.

Overall, how would you describe patient engagement in periodontal care? How do patients typically engage in the initial assessment of their periodontal status? What have you observed and concluded about patient attendance at periodontal clinical appointments? What have you noticed regarding patient compliance with treatment recommendations across periodontal therapies, including non-surgical, surgical, and supportive treatments? Overall, what communications challenges have you identified when interacting with patients undergoing periodontal care?

The survey and focus group interview guides for each stakeholder group will be pilot tested with similar others using standardized approaches. Data from the survey and focus groups will cover patient engagement (e.g., attendance at clinical appointment, compliance with treatment recommendations) across all critical phases of periodontal care, including referral, initial assessment, active treatment, and maintenance. Demographic information will be obtained to describe participants and ensure that vulnerable populations within the patient group are adequately represented. We anticipate ~ 600 uncertainties upon completion of this step.

### Step 3. Summarizing the research uncertainties

All the uncertainties or questions obtained through the survey and focus groups will be reviewed, sorted, and turned into indicative questions by members of the research team, and will later be discussed with the SC. Reviewing suggested uncertainties will include removing duplicate and similar uncertainties, excluding unrelated uncertainties, combining related uncertainties, and turning complex uncertainties into specific uncertainties. Sorting uncertainties will include coding and grouping them into categories within main engagement issues (e.g., referral, adherence). Lastly, uncertainties will be re-worded, if necessary, into single, indicative questions to improve clarity and understanding. Although unrelated uncertainties will be excluded from this study, they will be considered for future research by the team and shared with the broader research community through a non-original article, such as a letter to the editor or a short communication paper, in a periodontology-related journal. We expect approximately 100 engagement-related uncertainties upon completion of this step.

### Step 4. Verifying unanswered uncertainties

Given that the available literature on patient engagement in SPC has not been comprehensibly summarized and previous reviews have served different purposes, the research team will conduct a scoping review to map the breadth and depth of the research activity on this topic. This review will be used to verify whether the identified uncertainties have been answered and will include a quality assessment of the included studies. While this assessment is optional in scoping review studies, it will be necessary to assess whether the available evidence is credible enough to answer the suggested uncertainties. The quality assessment will be performed using design-specific critical appraisal tools (e.g., for cohort studies) and grading systems [38]. The scoping review will be initiated in step 1 to enable the utilization of the review findings in this step. Arksey & O’Malley’s multi-step framework will guide the scoping review [39], which will be reported according to the PRISMA Extension for Scoping Reviews guidelines [40]. Specifically, this review will characterize the types, sources, quality, and coverage of the available evidence to establish the existing knowledge and gaps in the literature. The assessment of the existing knowledge will be complemented by consulting previous reviews, position statements, and clinical guidelines related to patient engagement in periodontal services, including the referral process. Uncertainties already answered will be excluded, while unanswered or partially answered questions will be considered in the next step. We expect 60 to 70 unanswered or partially answered uncertainties upon completion of this step.

### Step 5. Completing an interim priority setting survey

Respondents of the survey who provided contact information will be invited to complete a second REDCap survey, which will include the remaining uncertainties from Step 4. They will be asked to rank their top ten uncertainties based on perceived relevance for patient engagement in SPC. Uncertainties included in this survey will be organized by engagement issue and randomly order within each issue. This survey will remain available for two months based on times allocated for completion in previous studies [41,42]. Responses from each participant will be recorded as follows: an uncertainty ranked 1 will be given 10 points, an uncertainty ranked 2 will be given 9 points, and so on down to an uncertainty ranked 10, which will be given 1 point. Total points per research uncertainty will be calculated to rank them from highest to lowest across engagement issues. We anticipate approximately thirty uncertainties upon completion of this step.

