### Step 6. Facilitating a priority setting workshop

All participants involved in steps 2 and 5 will be invited to participate in an in-person workshop to discuss, refine, and rank the top ten research uncertainties from the priority list generated in the previous step. Potential participants will be informed about the workshop’s purpose, benefits, risks, and their role, as well as the roles of other participants, such as the facilitator and members of the SC. Approximately 20 participants representing all the stakeholder groups are expected to be involved. We do not anticipate excluding any individuals who wish to participate at this stage, as our resources allow us to accommodate additional participants if necessary. Members of the SC will observe the workshop, which is expected to last approximately 2 hours. The workshop will be conducted by a facilitator trained in using the nominal group technique to build consensus [43], and will take place at the School of Dentistry at the University of Alberta. Workshop participants will receive tokens of appreciation (e.g., $25 gift card) for their involvement. The SC will review the top ten research priorities to further improve their wording in order to ensure understanding and facilitate dissemination.

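### People who joined only a focus group supply uncertainties and may attend the workshop, but have no stated vote in the interim ranking that fixes the workshop's list

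*Protocol article*

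**What the plan says.** The protocol article describes two sources of uncertainties under Step 2. One is an online REDCap survey with open-ended questions. The other is a set of focus groups: "Five focus groups with patients and six with different care provider groups (~7 participants in each focus group"). Step 3 pools the two: "All the uncertainties or questions obtained through the survey and focus groups will be reviewed, sorted, and turned into indicative questions".

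After the evidence check in Step 4, the article expects 60 to 70 items to remain. Step 5 puts these to an interim ranking survey, with this invitation rule: "Respondents of the survey who provided contact information will be invited to complete a second REDCap survey". Each voter ranks ten items, points are summed, and the list is shortened: "We anticipate approximately thirty uncertainties upon completion of this step".

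Step 6 uses a wider rule: "All participants involved in steps 2 and 5 will be invited to participate in an in-person workshop". The workshop works from the list that Step 5 produced, and its expected size is small: "Approximately 20 participants representing all the stakeholder groups are expected to be involved".

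Under Study strengths, the article describes its approach as one that gives equal consideration to the uncertainties of all stakeholders.

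**The concern.** The three steps treat focus-group participants differently. They are contributors at Step 2 and eligible to rank at Step 6, but the Step 5 rule does not reach them unless they also answered the first survey. No reason is given.

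Step 5 is where most items are lost to voting. An item that falls below the cut does not go to the workshop, so a later invitation cannot bring it back. At stake is who determines the shortlist: if some contributors raised questions that survey respondents rank low, those questions drop out without the people who raised them having voted. This sits poorly with the equal-consideration statement, although that statement concerns uncertainties and does not itself promise every contributor a vote.

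**Working it through.** **1. The invitation rules side by side**

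| Step | Role | Survey respondents | Focus-group-only participants |
|---|---|---|---|
| 2 | Supply uncertainties | Yes | Yes |
| 5 | Rank 60–70 items, leaving about 30 | Yes, if contact details were given | No stated route |
| 6 | Set the top ten from the Step 5 list | Invited | Invited |

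The word *survey* in Step 5 cannot readily be stretched to cover focus groups. Step 2 describes them as separate methods, and Step 3 names them as two sources.

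**2. What the Step 5 cut removes**

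60 − 30 = 30 and 70 − 30 = 40, so about 30 to 40 items leave the process at this vote.

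**3. How many people are affected**

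Inputs from Step 2: 5 patient groups and 6 provider groups of about 7.

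- Patients: 5 × 7 = 35
- Providers: 6 × 7 = 42
- Total: 35 + 42 = 77. The article does not state this total; it follows from its figures.

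Let v be the share of focus-group participants who also answered the first survey. The article does not give v, so it is varied over its whole range. The number with no stated vote is 77 × (1 − v).

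**4. As a share of contributors**

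Research setting and participants gives planned enrolment by group: "we estimate the enrollment of ~ 150 patients, ~ 60 general dentists, ~ 20 periodontists, and ~ 30 dental hygienists". The sum is 150 + 60 + 20 + 30 = 260. The article does not say whether this means survey respondents alone or everyone including focus groups, so both readings are shown.

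- Reading A (260 are survey respondents, focus-group-only participants are extra): share = 77(1 − v) / [260 + 77(1 − v)]
- Reading B (260 is everyone): share = 77(1 − v) / 260

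| Assumed overlap v | No stated vote | Share, reading A | Share, reading B |
|---|---|---|---|
| 0% | 77 | 77/337 = 23% | 77/260 = 30% |
| 25% | 58 | 18% | 22% |
| 50% | 38–39 | 13% | 15% |
| 75% | 19 | 7% | 7% |
| 100% | 0 | 0% | 0% |

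The abstract gives a different provider total: "Study participants will be periodontal patients (n ~ 150) and care providers (n ~ 120"). That makes 150 + 120 = 270, against 60 + 20 + 30 = 110 providers and 260 overall in the methods. With 270, the zero-overlap shares become 77/347 = 22% and 77/270 = 29%, so the conclusion does not depend on which total is right.

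**5. Effect of aligning the rules**

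With v = 0, the Step 5 invitation list rises from at most 260 to at most 337 (reading A), or from at most 260 − 77 = 183 to at most 260 (reading B). With v = 1 it does not change.

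**The case against.** **The number affected may be small or zero.** Survey and focus groups sit in one step, serve the same stakeholder groups and share recruitment channels. Many focus-group participants may also complete the survey. This stands: 77 is a ceiling, and a reader who takes it as the number shut out goes beyond the article.

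**The Step 5 sentence does not say *only*, and this is a condensed article.** It is true that the sentence does not expressly close the vote to others. But it states who is invited, and Step 6 shows that the article writes a broader rule when it means one. What is raised is a mismatch between two stated rules, not a missing detail.

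**Focus-group participants are invited to the workshop.** Correct, and they are not excluded from the final ranking. But the workshop ranks the list left by Step 5, so the invitation does not restore a say in what was cut.

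**Returning to the same respondents is a coherent design.** It is, and needing contact details for an invitation is unavoidable. Neither point explains why one group of Step 2 contributors is left out.

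Two stronger readings are tempting, and the article supports neither:

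- *That the rule works against older or low-income patients.* Nothing says that focus groups target them, and the groups may run on Zoom. For bias from internet access, Study limitations proposes considering other ways of taking the survey (paper, telephone, in person). People reached that way count as survey respondents. Focus groups are named there for a different problem, uneven participation and ability to articulate uncertainties.
- *That the voting panel will be very small in some professions.* Any such count needs rates for leaving contact details and for responding, and the article gives neither. Small numbers of periodontists and hygienists follow mainly from planned enrolment of about 20 and 30, not from the invitation rule.

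**Conclusion.** The point holds in limited form. As written, anyone who took part only in a focus group has no stated vote in the ranking that cuts 60–70 items to about 30, although Step 3 uses their uncertainties and Step 6 invites them. The number is between 0 and about 77. At zero overlap this is 23% of contributors if the 260 are all survey respondents, or 30% if the 260 include the focus groups.

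The structural conclusion rests only on the stated rules. Its size rests on the unstated overlap and on groups filling to about 7. Whether the shortlist would differ cannot be judged from the article. The change is worth making before Step 5 opens, because it concerns who sets the shortlist.

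**What to change.** Replace the Step 5 invitation rule with: *All Step 2 participants (survey and focus groups) who provided contact information will be invited to complete the second REDCap survey.* This brings it into line with Step 6. Ask focus-group participants whether they also answered the first survey, record the overlap, and report it with the number of people invited from each source.

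The cost is one sentence, a slightly longer mailing list and probably a minor ethics amendment. The team must be able to reach focus-group participants in any case: Step 6 invites them to the workshop, and the Dissemination section plans to email them the results. If the overlap proves complete, the invitation list does not change. Recruiting new voters is not needed to resolve the mismatch.

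### The interim survey states random order only within engagement issues but ranks points across them, so a position effect between issues is uncontrolled if all respondents see the issues in one order

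*Protocol article*

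**What the plan says.** Step 5 describes the interim survey. Its list is what remains after Step 4, where the article says: "We expect 60 to 70 unanswered or partially answered uncertainties upon completion of this step". The layout is given in one sentence: "Uncertainties included in this survey will be organized by engagement issue and randomly order within each issue". The response task is: "They will be asked to rank their top ten uncertainties based on perceived relevance for patient engagement in SPC". For scoring, "an uncertainty ranked 1 will be given 10 points, an uncertainty ranked 2 will be given 9 points", and so on down to 1 point for rank 10. The points are then used as follows: "Total points per research uncertainty will be calculated to rank them from highest to lowest across engagement issues". The expected result is: "We anticipate approximately thirty uncertainties upon completion of this step".

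The article does not say in what order the issues appear, or whether that order is the same for everyone. It does not say whether the order inside an issue is drawn for each respondent or once for all. Neither Step 5 nor the section Data management and analysis mentions a check or correction for position.

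The number of issues is not given. Step 3 offers referral and adherence as examples, and Step 2 lists four phases of care: "including referral, initial assessment, active treatment, and maintenance".

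Under Step 6, the shortened list goes to a facilitated workshop, which settles the ten priorities.

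**The concern.** The stated randomisation and the decisive comparison are at different levels. Drawing a random order inside an issue gives every item of that issue the same expected position. It leaves the expected positions of items in different issues unequal, and those are the items whose totals are compared when the list is cut.

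The task is open to such an effect. Each respondent names ten of 60 to 70 items, and an item outside the ten adds nothing to its total. An item skimmed or never reached therefore scores the same as one read and rejected.

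Three things would be at stake if the block order is shared:

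- Any advantage of early blocks would be systematic, so more respondents would not reduce it.
- Position and issue would be confounded, so the effect could not be separated from real preference afterwards.
- The cut keeps only 30/70 = 43% to 30/60 = 50% of the items, and the article describes no route by which a dropped item returns. This sits badly with the claim under Study strengths that all stakeholders' uncertainties receive equal consideration.

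**Working it through.** The article has no figure of its own to reproduce here, since it states no sample size calculation. The check asks how far a position effect could move the cut, and whether varying the block order removes it.

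**Inputs from the article**

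- Items on the list: 60 to 70 (Step 4).
- Points per respondent: 10 + 9 + … + 1 = 55 (Step 5). The sum is fixed, so a gain for one block is a loss for the others.
- Items kept: about 30 (Step 5).
- Respondents: at most 150 + 60 + 20 + 30 = 260 (Research setting and participants). The number answering the interim survey is not given, and only first-survey respondents who left contact details are invited.

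**Assumptions, not in the article**

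- Four issue blocks.
- Item quality with SD 0.3 on the log-odds scale.
- A linear position effect b from the first to the last place on the list, with b = 0, 0.25, 0.5 or 1.0.

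**Model.** With M items and position running from 0 to M − 1, a respondent's preference for an item is quality + Gumbel noise + b × (1 − position/(M − 1)). The ten highest get 10 to 1 points, totals are summed, and the top 30 are kept. Order within blocks is random for each respondent throughout. Each setting was simulated 200 times.

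To read b: of two equally good items in first and last position, the first is preferred with probability 1/(1 + e^(−b)). That is 56%, 62% and 73% for b = 0.25, 0.5 and 1.0.

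**Result with one shared block order (60 items, 260 respondents, four blocks of 15)**

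| b | First block: share of points | First block: places of 30 | Last block: share of points | Last block: places of 30 |
|---|---|---|---|---|
| 0 | 25% | 7.5 | 25% | 7.5 |
| 0.25 | 27.2% | 9.1 | 22.7% | 5.8 |
| 0.5 | 29.6% | 10.6 | 20.4% | 4.2 |
| 1.0 | 34.5% | 13.1 | 16.8% | 1.9 |

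**Hand check of the last row.** The mean positions of the four blocks are 7, 22, 37 and 52 of 0 to 59. The mean bonuses at b = 1.0 are 1 − 7/59 = 0.881, then 0.627, 0.373 and 0.119. Their exponentials are 2.41, 1.87, 1.45 and 1.13, which sum to 6.86. The first-choice shares are then 2.41/6.86 = 35% for the first block and 1.13/6.86 = 16% for the last, close to the simulated 34.5% and 16.8%.

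**Result with block order drawn for each respondent.** Every block gets about 25% of the points and 7.4 to 7.7 of the 30 places at every b tried.

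**Other settings, shared order, first block, b = 0 to b = 1.0**

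- 65 items (blocks of 17, 17, 17 and 14), 260 respondents: 26.4% to 35.9% of points, 7.9 to 14.1 places.
- The same with 130 respondents: 26.1% to 35.8%, 7.9 to 13.5 places. The shift is about the same at either number.
- 70 items (blocks of 18, 18, 18 and 16), 260 respondents: 25.7% to 35.8%, 7.6 to 14.6 places.

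**The case against.** The strongest reply is that the key premise is not in the text. Step 5 is silent on the order of the issues, and this is a condensed article, which may leave the build of a form to a fuller document. That stands as a limit on the claim. It does not remove it: the article does choose to state where randomisation applies, and it names one level only.

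A reader might infer that the issue listed first gains points from position alone, or that late items are seen only by those who scroll to the end. The documents support neither. They give no primacy effect, page layout or drop-off rate, and respondents are asked to choose from the whole list. With no effect, the gain is zero.

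A reader might also infer that the bias passes straight into the final ten. It does not. The survey is a coarse screen, and the workshop discusses and ranks what survives. What remains is the harm to items that position pushes below the cut, because the workshop works from the shortened list.

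Finally, four blocks and the values of b are assumptions. That stands too. The figures show a range and do not estimate what will happen.

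**Conclusion.** The point holds in conditional form. The article states random order within issues only, while the cut from 60–70 to about thirty is made on totals across issues. If the issue order is shared by all respondents, nothing in the plan controls a position effect between issues, and the data could not show it afterwards.

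The size cannot be derived from the documents. Under the four-block, 60-item, 260-respondent assumptions, the first block's excess runs from nothing to 34.5 − 25 = 9.5 percentage points of the points, or from nothing to 13.1 − 7.5 = 5.6 of the thirty places. The upper ends need a strong assumed effect; at b = 0.25 the excess is 9.1 − 7.5 = 1.6 places.

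This is not a demonstrated bias. It is an inexpensive improvement that protects the comparison the survey is used for, and it must be made before the survey opens.

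**What to change.** Add to Step 5 that the order of the issue blocks is also randomised or rotated across respondents. If that is already intended, one sentence saying so is enough.

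- **Block order.** Either draw it for each respondent, or prepare as many survey versions as there are issues once these are known, in a Latin-square order assigned at random with the invitation. The number of versions should not be set at four in advance.
- **Order within blocks.** Keep it at least as fine as now planned. If it is to be drawn for each respondent, versions should not reduce it to one order per version.
- **Record and check.** Store the version and compare points by version for whole blocks only. Item-level comparison would be too thin: with four versions, at most 260/4 = 65 respondents see each, which gives 65 × 10/70 = 9.3 to 65 × 10/60 = 10.8 selections per item and version.

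The cost is a few copies of the REDCap form, one version variable and a short set-up time. The number of respondents and the scoring rule stay as they are.
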